### Eligibility criteria

#### Inclusion criteria

At least 24 hours of invasive mechanical ventilation.Age ≥18 years.Patient is mechanically ventilated in a ventilator mode, and by a ventilator, supported by the BEACON Caresystem.Haemodynamically stable, where instability is defined by the presence of two or more of the following criteria: acidosis pH <7.2, poor urine output <0.5 mL/kg/h, use of vasopressors, for example, noradrenaline >25 µg/min.

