### Primary and secondary outcomes

The primary outcomes include:

Duration of mechanical ventilation to successful extubation defined as the time from the start of mechanical ventilation, defined as either the time of intubation in the ICU, or the time of admission to the ICU following previous intubation for surgery, and until successful extubation, with successful extubation defined as ≥48 hours of unassisted spontaneous breathing after extubation.

Unassisted spontaneous breathing is defined here to include supplementary oxygen and support with high-flow nasal catheters. Patients with non-invasive mask ventilation are considered to be assisted.

The secondary objectives of the trial are to compare the following variables in the standard care group and BEACON Caresystem group:

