Duration of mechanical ventilation to successful extubation following randomisation defined as the time from randomisation and until successful extubation, with successful extubation defined as ≥48 hours of unassisted spontaneous breathing after extubation.Time from control mode to support mode defined as the time following randomisation, from initiation of control modes of ventilation and until initiation of support modes of ventilation.Time from support mode to successful extubation defined as the time following randomisation, from initiation of support modes of ventilation and until successful extubation.Number of changes in ventilator settings per day defined as the daily registered number of changes to ventilator settings from randomisation until successful extubation.Time to first SBT defined as the time from randomisation to the first performed SBT.Time to first successful SBT defined as the time from randomisation to the first successful SBT.Time to first extubation defined as the time from randomisation to the first extubation attempt.Time to first disconnection from mechanical ventilation defined as the time from randomisation to the point at which mechanical ventilation is first discontinued.Percentage of time in control mode ventilation defined as the time from randomisation which is spent in controlled modes of mechanical ventilation in per cent of duration of mechanical ventilation.Percentage of time in support mode ventilation defined as the time from randomisation which is spent in support modes of mechanical ventilation in per cent of duration of mechanical ventilation.Use of sedatives defined as the cumulative use of sedative drugs from randomisation until successful extubation.Use of neuromuscular blockading agents defined as the cumulative use of neuromuscular blockading agents from randomisation until successful extubation.Number of intubation free days defined as the number of days without intubation from randomisation until successful extubation.Number of reintubations defined as the number of reintubations following extubation from randomisation until successful extubation.Number of tracheostomies defined as the number of patients having tracheostomy performed from randomisation until successful extubation or protocol end.Number of patients on prolonged mechanical ventilation defined as the number of patients on mechanical ventilation ongoing for more than 21 days after the start of mechanical ventilation.Number and types of adverse events related to mechanical ventilation defined as the incidence of adverse events directly related to mechanical ventilation.ICU mortality defined as the mortality from randomisation and until death or ICU discharge.Length of stay defined as the duration of ICU admission from the start of mechanical ventilation and until death or ICU discharge.Mobilisation times defined as the time from randomisation until (1) first mobilisation, for example, sitting on the edge of the bed, standing up and marching on the spot and (2) regaining independency, for example, able to drink/eat or comb hair.Daily patient physiological blood gas status defined as daily ABG values of SaO_2_, PaO_2_, PaCO_2_, pH from randomisation until successful extubation.Daily average physiological status defined as daily averages of measured values of oxygenation (SpO_2_), end-tidal CO_2_ fraction (EtCO_2_), ventilation (respiratory rate, tidal volume, anatomical dead space), pulmonary mechanics (airway pressure, respiratory system compliance) and ventilator settings as measured routinely at the bedside.

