The results of this study compare care provided with the system’s advice with current clinical practice at study sites. As there is no standard of care or usual method of weaning in the UK, this study does not compare the system’s advice with that of best practice defined by clinical guidelines. To avoid comparing two interventional changes, no attempt will be made to standardise care in the control arm according to best practice.

As patients are studied for many days, it is not possible to store continuous waveform data for all patients at all times. Systematic analysis of patient-ventilator asynchrony will not therefore be possible.

This study excluded patients if ventilated for <24 hours. In doing so, patients ventilated post surgery defined previously as simple to wean are not included. This should not imply that the patients studied here are necessarily difficult to wean, but rather that they represent a broad cross section of mechanically ventilated patients not simply recovering from the effects of anaesthesia.

In addition, it is important to note that substantial training has been provided to all sites in the use of the BEACON Caresystem and the same clinical team treat patients for both the control and intervention arm. It is possible then that both training and use of the system influence routine care, potentially biasing study results.

This paper describes the study protocol of a randomised control trial evaluating the advice of the BEACON Caresystem in a general medical ICU population. This protocol represents an important step evaluating the use of advice over the whole of the ICU stay, and only in patients intubated greater than 24 hours. The results will indicate whether the BEACON Caresystem is a useful tool in optimising ventilation strategy.

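### Intubation-free days stop being counted at successful extubation, so the outcome cannot show earlier extubation and tends to favour the arm with more failed extubations

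*Protocol article*

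**What the plan says.** All the definitions are in the protocol article under Primary and secondary outcomes, unless another section is named.

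- Intubation-free days: "Number of intubation free days defined as the number of days without intubation from randomisation until successful extubation".
- Success is tied to 48 hours off support: "with successful extubation defined as ≥48 hours of unassisted spontaneous breathing after extubation". Oxygen and high-flow nasal support are allowed in that period, but "Patients with non-invasive mask ventilation are considered to be assisted".
- Patients are intubated at entry. Inclusion criteria require "At least 24 hours of invasive mechanical ventilation", and the Discussion confirms it: "This study excluded patients if ventilated for <24 hours".
- Reintubations have the same stop: "Number of reintubations defined as the number of reintubations following extubation from randomisation until successful extubation".
- Percentage of time in control mode is "the time from randomisation which is spent in controlled modes of mechanical ventilation in per cent of duration of mechanical ventilation", and support mode is worded in parallel. The denominator has no stated start. The primary outcome, "Duration of mechanical ventilation to successful extubation defined as the time from the start of mechanical ventilation", has its clock running before randomisation. The first secondary outcome defines a version that starts at randomisation.

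Two other statements bear on the window. Statistical considerations says that outcomes are measured over the whole protocol, and the section on the spontaneous breathing trial ends the protocol at ICU transfer, ICU discharge or death. Of the outcomes that stop at successful extubation, only the tracheostomy count adds protocol end as an alternative stop.

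**The concern.** An intubation-free-days outcome should reward getting the tube out sooner and keeping it out. That credit comes from the time after the last extubation, and this definition cuts that time off. What is left is mainly time off the tube that did not lead to success: the gap between a failed extubation and reintubation, or a spell on mask ventilation.

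The trial's hypothesis is a shorter time to successful extubation. On this outcome, an arm that extubated everyone sooner at the first attempt would look identical to one that extubated everyone late at the first attempt. An arm with more failed attempts could look better. A reader of the results table would take more intubation-free days as benefit.

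Two neighbouring definitions raise smaller questions of the same kind: where the reintubation count stops, and where the denominator of the mode percentages starts.

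**Working it through.** The plan gives no figure for these outcomes, so there is none to reproduce. Its sample size, 137 per arm, rests on duration of ventilation and does not enter here. The check is to score patient courses under the definition as written.

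**Intubation-free days.** Time runs from randomisation, with every patient intubated at time 0. The courses are invented for illustration. The score is the tube-free time before success, plus 2 days if the window is taken to close when the 48 hours are complete. The last column counts tube-free days to day 28, a horizon assumed here only for comparison.

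| Course | Closes at successful extubation | Closes at 48 h confirmation | To day 28 |
|---|---|---|---|
| A. First extubation succeeds at 3 days | 0 | 0 + 2 = 2 | 28 − 3 = 25 |
| B. First extubation succeeds at 20 days | 0 | 0 + 2 = 2 | 28 − 20 = 8 |
| C. Extubated at 3 days, off the tube 1.5 days, reintubated for 8 days, then success | 1.5 | 1.5 + 2 = 3.5 | 28 − 3 − 8 = 17 |
| D. Extubated at 3 days to mask ventilation for 4 days, then unassisted | 4 | 4 + 2 = 6 | 28 − 3 = 25 |

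On either closing rule A and B tie, although B was intubated 17 days longer, and C and D score above both. With a fixed horizon, A again scores above C and C above B. In the first score column, D takes success to begin when mask support ends. If success were dated to removal of the tube, D would score 0 there; A, B and C would not change.

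**Arm means.** Closing at extubation and ignoring mask ventilation, the arm mean is f × m, where f is the share of patients with a failed extubation and m the mean tube-free days per failure. The documents give neither, so a range is assumed:

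- f = 5%, m = 0.5: 0.05 × 0.5 = 0.025 days.
- f = 20%, m = 1.5: 0.20 × 1.5 = 0.30 days.
- At m = 1, f = 10% gives 0.10 days and f = 20% gives 0.20 days, so the arm with twice the failures has the higher mean.

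Time to extubation does not appear in the formula.

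**Mode percentages.** Suppose the denominator T starts with ventilation and p days pass before randomisation. Control plus support can then reach at most (T − p)/T. The values of p are assumptions, with 1 day suggested by the 24-hour entry criterion. For T, 7.2 days is the plan's historical mean, 5.2 is that mean less the planned 2-day improvement, and 3 is a short stay.

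| T (days) | p = 1 | p = 2 |
|---|---|---|
| 7.2 | 86.1% | 72.2% |
| 5.2 | 80.8% | 61.5% |
| 3 | 66.7% | 33.3% |

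If the denominator starts at randomisation, p = 0 and there is no shortfall.

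**The case against.** The strongest reply is that this is one of 22 secondary outcomes, and that shorter ventilation is also measured by time from randomisation to successful extubation and by time to first extubation. The general sentence about measuring over the whole protocol suggests that the stop was carried over from neighbouring items in drafting. This stands as a limit on the consequences. It does not rescue the definition, because a general sentence does not override a specific stop, and the tracheostomy item shows that protocol end was added where it was wanted.

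Several stronger readings are tempting, but the documents do not support them:

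- That a higher score always means a worse course. A patient who is never extubated and dies intubated also has no tube-free days, so the worst course can tie with the best. The outcome is uninformative and partly perverse, not cleanly reversed.
- That first-time successes necessarily score 0. They share one value, which is 0 or 2 days depending on when the window closes.
- That the reintubation count is an error. As a count of failures before success it is coherent. It leaves out reintubations after 48 hours of unassisted breathing, although follow-up continues and reintubation is documented. Nor does the article call late reintubation the main safety cost of the system. It says that the system does not suggest extubation and that this decision follows standard practice in both arms.
- That the mode percentages cannot sum to 100. That follows only if the denominator starts before randomisation. The article also defines a post-randomisation duration, so this is an ambiguity.

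**Conclusion.** The point holds for intubation-free days. As defined, every patient whose first extubation succeeds gets the same value, however long that took, while a failed extubation, or extubation to mask ventilation, adds days. Patients never successfully extubated have no stated end of window. The outcome cannot show earlier extubation and tends to favour the arm with more failed extubations.

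That conclusion needs only the stated window and intubation at entry, and it survives both readings of when the window closes. The credit for mask ventilation also rests on success not being dated until mask support ends. The arm means of 0.025 to 0.30 days rest on assumed failure rates and show scale only.

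The late-reintubation gap and the unclear denominator are lesser wording points. All three concern secondary outcomes; the primary outcome and sample size are untouched.

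**What to change.** Redefine intubation-free days as days alive and not intubated from randomisation to a fixed horizon chosen by the sponsor, using data to protocol end. Score death in ICU as 0, and count patients who leave ICU alive and extubated as free from then to the horizon. The downside is that last assumption: the Discussion says patients are not followed after ICU transfer, so later deaths and reintubations are unknown. It should be stated with the definition and again with the result. Counting only to protocol end would avoid the assumption, but the horizon would then differ between patients.

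Alongside this:

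- Keep the count of reintubations before success and add reintubations after 48 hours up to protocol end.
- State that both mode percentages use ventilated time from randomisation as denominator.

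The cost is a change of outcome wording and a matching registry update, dated before outcomes are compared by arm. No new data collection is needed, since everything is drawn from the existing ICU follow-up.

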### Study design

To test the hypothesis that following advice from the BEACON Caresystem will reduce time to successful extubation, the Intenive Care weaning (iCareWean) group has designed a single-blinded multicentre randomised control trial evaluating management of mechanical ventilation as directed by the BEACON Caresystem compared with that of current care in the general intensive care setting. The Consolidated Standards of Reporting Trials (CONSORT) flow diagram of the study is illustrated in figure 1.

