#### Spontaneous breathing trial (SBT)

During weaning from mechanical ventilation, the BEACON Caresystem monitors the levels of Pressure Support (PS) and Positive End Expiratory Pressure (PEEP). When these levels are reduced to values below clinical guideline thresholds,^21^ the BEACON Caresystem automatically monitors variables evaluating spontaneous breathing criteria. If these remain within limits and for a duration determined by international guidelines,^21^ the system prompts the user to assess the appropriateness of extubation and provides a checklist to help. The primary function of the BEACON Caresystem with regards weaning is to reduce levels of support where possible; it does not suggest an active SBT or extubation. As such, the decision to extubate is according to standard clinical practice for both arms of the study, meaning that at any time the clinical team can perform an active SBT or extubate the patient without confirmation from the system. Reintubation is documented by the research team and the participant enters a standard care pathway, which involves the deactivation of the BEACON Caresystem. The participant is then followed up until the end of the protocol (figure 1).

The protocol ends with transfer or discharge from ICU or death (figure 1).

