
### Statistical considerations

Sample size was determined by a power analysis of duration of mechanical ventilation. Extrapolation of the 2016 ICU admission data from two London-based NHS hospitals provided a sample size of 548 patients over an 18-month period. In these patients, mean total duration of mechanical ventilation measured in days was 7.2, with an SD of 7.0 days. A study population of 137 patients in each randomisation group would allow detection of a 2 day or 30% improvement in the duration of mechanical ventilation in the BEACON Caresystem group assuming a similar improvement in SD, with an α level of 0.05 and power of 0.8. A 2 days or 30% reduction in duration of mechanical ventilation is similar to that used previously.^6^

Primary and secondary outcomes will be measured across the protocol duration and comparison made by independent samples t-test, or appropriate non-parametric testing if not normally distributed. Complementary analysis will be performed using Kaplan-Meier curves.

The study is not sufficiently powered to allow subgroup analysis for the groups specified in the randomisation strategy.

An independent data safety monitoring committee will be established as part of the study, with this committee responsible for defining stopping criteria. Safety data will be looked at after the first 80 patients have been recruited, with an interim analysis performed following 50% recruitment.

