## Safety, ethics and dissemination

### Adverse events

All adverse events will be monitored and documented until the end of study. Adverse events are reported to the trial sponsor according to their standard operating procedure for further investigation. As patients are critically ill, it is expected that unrelated adverse events will occur as part of hospital stay. Adverse events are therefore only defined in relation to changes in mechanical ventilation, for patients allocated to either the control or intervention arms.

Serious adverse events are defined as:Death, suspected to be caused directly by the settings of mechanical ventilation.Adverse events include the following events suspected to be caused directly by the settings of mechanical ventilation:Pneumothorax.Self-extubation.Hypoxaemia (SpO_2_ <90%; PaO_2_ <8.00 kPa).Alkalaemia (pH >7.5).Acidaemia (pH <7.2).

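### The ventilator-related adverse-event outcome has no ventilated-time denominator, so on its own it cannot show whether ventilation under the device's advice is more hazardous per day

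*Protocol article*

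**What the plan says.** All of this is in the protocol article.

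- **Primary and secondary outcomes** gives the adverse-event outcome as "Number and types of adverse events related to mechanical ventilation defined as the incidence of adverse events directly related to mechanical ventilation". No unit of exposure is attached. The same list does scale other outcomes to time: ventilator-setting changes are counted per day, and time in control or support mode is a percentage of ventilation duration.
- **Statistical considerations** fixes window and test together: "Primary and secondary outcomes will be measured across the protocol duration and comparison made by independent samples t-test", or a non-parametric test where the data are not normal. Kaplan-Meier curves are named as complementary.
- **Spontaneous breathing trial (SBT)** sets the end of the window: "The protocol ends with transfer or discharge from ICU or death".
- **Adverse events** restricts what is counted: "Adverse events are therefore only defined in relation to changes in mechanical ventilation, for patients allocated to either the control or intervention arms". The list is introduced by "Adverse events include the following events suspected to be caused directly by the settings of mechanical ventilation" and covers pneumothorax, self-extubation, hypoxaemia, alkalaemia and acidaemia.
- **Study design** states the aim: "To test the hypothesis that following advice from the BEACON Caresystem will reduce time to successful extubation". The sample-size paragraph assumes a mean of 7.2 days (SD 7.0) and a reduction of 2 days or 30%, with 137 patients per arm.

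**The concern.** An event attributed to ventilator settings can arise essentially only while the patient is ventilated. The trial is designed in the expectation that one arm will have less of that time. A comparison of events per patient therefore combines two things: how hazardous a day of ventilation is, and how many such days there are. If the device works as hypothesised, an unchanged daily hazard appears as fewer events, and a materially higher daily hazard can appear as no difference.

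The distinction matters here. The section on safety considerations makes application of the advice mandatory, and it accepts that inappropriate setting changes, if applied, can have serious consequences. Whether ventilation under the advice is more or less hazardous per day than under standard care is a question a reader will want the trial to answer. The listed outcome, taken alone, does not answer it.

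**Working it through.** **Plan's own figure.** The stated size is 137 per arm for a 2-day difference, power 0.8 and α 0.05 (two-sided assumed). Reading the similar improvement in SD as 30% gives 7.0 and 4.9 days, average (7.0 + 4.9)/2 = 5.95. Then n = 2 × (1.96 + 0.84)² × 5.95² / 2² ≈ 139 per arm, and power at 137 is 0.794. That agrees closely enough. The point does not depend on this figure; the design durations are used only to size the effect.

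**Break-even daily rate.** If events occur at rate λ per ventilator-day and mean ventilated time is T, expected events per patient are λT. The arms show equal events per patient when λ(device)/λ(control) = T(control)/T(device).

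| Ventilated time, control v device | Basis | Break-even rate ratio |
|---|---|---|
| 7.2 v 5.2 days | 2-day reduction | 7.2/5.2 = 1.38 |
| 7.2 v 5.04 days | 30% reduction | 7.2/5.04 = 1.43 |
| 6.2 v 4.2 days | 2-day reduction, 1 day removed | 6.2/4.2 = 1.48 |
| 6.2 v 4.04 days | 30% reduction, 1 day removed | 6.2/4.04 = 1.53 |

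Removing 1 day is an assumption. It reflects the inclusion criterion of at least 24 hours of ventilation before entry. None of these ratios needs an event rate.

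In the other direction, with an identical daily rate the device arm would show 1 − 4.2/6.2 = 32% fewer events per patient.

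**Simulation.** The protocol gives no event rate, so 0.05, 0.1 and 0.2 events per ventilator-day are assumed. There are 137 patients per arm, with lognormal at-risk time of mean/SD 6.2/7.0 (control) and 4.2/5.06 (device; 7.0 × 5.2/7.2 = 5.06). Each setting has 2,000 runs. Events are Poisson, either without extra variation or with strong between-patient clustering (gamma frailty, variance 1). The per-patient t-test on counts is set beside a comparison of rates per ventilator-day with robust variance. Ranges run from the lowest to the highest assumed rate.

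| True daily rate ratio | Clustering | t-test on events per patient | Robust rate comparison |
|---|---|---|---|
| 1.48 | none | rejects in about 5% | detects in 43%, 71%, 95% |
| 1.48 | strong | rejects in about 5% | detects in 31%, 40%, 49% |
| 1.00 | none | favours device in 29%, 41%, 55% | rejects in about 5 to 6% |
| 1.00 | strong | favours device in 23%, 26%, 33% | near nominal, slightly high at 0.2 per day |

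At a 1.48-fold daily rate, the per-patient test therefore rejects no more often than its false-positive level. That is what it should do, since the mean counts are equal. It is answering a different question.

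The choice of test matters. A simple binomial rate test that ignores clustering had a false-positive rate of 18% at frailty variance 1 and 25% at variance 2 (0.1 events per day). The power figures above therefore use robust variance.

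**The case against.** **The protocol may not exclude a rate.** The word incidence can mean a proportion, a count or a rate, and the t-test sentence is a blanket statement for more than 20 outcomes. This stands in part: a rate is not expressly excluded. But the article is not silent. It names the measure, the window and the test, and it scales neighbouring outcomes to time. The natural reading is an unadjusted comparison per patient.

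**Events per randomised patient is a valid measure.** This stands fully. It is protected by randomisation, and fewer events because of less ventilation is a real benefit. A reader might infer that the planned comparison is biased or should be replaced. The documents do not support that: the limitation is only that it cannot answer the per-day question alone.

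**The rate has weaknesses of its own.** It conditions on ventilated time after randomisation, which the device is meant to change. If easier patients come off sooner in the device arm, the remaining days belong to sicker patients. Self-extubation, a listed event, can itself end exposure. The rate also includes time with the system off, after reintubation or during a malfunction. All of this stands, and it is why the rate should be supplementary.

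**Other outcomes are daily.** Daily blood gases and daily averages of physiological measurements are compared between arms, and three of the five listed events are thresholds of such variables. This helps, but daily values and averages are not event rates, and they do not cover pneumothorax or self-extubation.

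**Two further inferences fail.** A reader might think that ICU time after extubation dilutes the comparison. Time that contributes no events adds nothing to a per-patient count and does not distort it. A reader might also conclude that the safety committee's looks would be misled. The article leaves stopping criteria to that committee and does not say which summary it will see.

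**Conclusion.** The point holds as a limitation of a valid outcome. As written, the adverse-event comparison cannot reveal a higher event rate per ventilator-day if ventilation is shortened. At the protocol's design effect, the excess compatible with equal events per patient is 38% (7.2/5.2), or 48% if one pre-randomisation day is removed (6.2/4.2).

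The ratios assume that the full design reduction occurs; with no shortening there is no masking, and with a smaller shortening there is less. The detection figures also rest on assumed event rates and duration distributions, and clustering lowers the power of the rate comparison considerably. The documents give no evidence that the device does carry a higher daily hazard. A pneumothorax might be detected after extubation, so confinement to ventilated time follows from the causal definition and is not absolute. Adding a rate is a cheap improvement that is worth making.

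**What to change.** In the adverse-event outcome, keep the per-patient incidence and add events per 100 ventilator-days from randomisation. Analyse the rate with a negative binomial model, or a Poisson model with robust variance, using log(ventilated time after randomisation) as the offset. Report the rate ratio with its 95% CI overall and, where numbers allow, by event type. State that the rate is supplementary and is read beside the per-patient figure.

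The cost is mainly analysis wording, because ventilation timing is already needed for the duration outcomes. The downside is two safety figures instead of one. The second conditions on a post-randomisation quantity and includes ventilated time when the system is off, and the text should say so.

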## Discussion

This paper presents the study protocol of single-blinded multicentre randomised control trial evaluating management of mechanical ventilation as directed by the BEACON Caresystem compared with that of standard care in the general intensive care setting. To test the hypothesis that following advice from the BEACON Caresystem will reduce time to successful extubation, patients are randomised to care including advice from the system, or standard care. In addition, as secondary outcomes, the study will investigate whether application of the advice changes the time spent in control ventilation modes, the number of changes made to the ventilator, the use of medication such as sedative or neuromuscular blocking agents, the changes in clinical procedures such as reintubation or tracheostomy and clinical and physiological status of the patient. Although not powered to detect differences between groups, it will also investigate the length of stay at the ICU and patient mortality.

This study is the next step in evaluation of the advice of the BEACON Caresystem. A large number of studies have been performed validating the physiological models included in the system, as summarised in,^9^ and studies of short duration have been performed evaluating the physiological response to application of advice.^14 15^ This use of the system over the whole duration of ICU stay allows for assessment of more meaningful clinical outcomes, relating to the time spent on mechanical ventilation. In addition, the study includes only patients intubated for a minimum of 24 hours, meaning that short-term postoperative patients who may have rather uncomplicated intubation periods are not included.

The study includes limitations. The study was powered on duration of mechanical ventilation rather than duration to successful ventilation, this being the historical data available during study design. The study is not powered to detect changes in mortality, and does not follow-up on the patients after transfer from the ICU. In the context of this study, successful extubation is defined as the lack of need for non-invasive ventilator support for 48 hours after extubation, rather than successful rehabilitation of the patient subsequent to their ICU stay.

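### ICU length of stay ends at death as well as at discharge and is compared directly between arms, so early deaths shorten it and can look like a benefit

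*Protocol article*

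**What the plan says.** The secondary outcomes are introduced as between-arm comparisons: "The secondary objectives of the trial are to compare the following variables in the standard care group and BEACON Caresystem group". Length of stay is one of them, in the Primary and secondary outcomes section: "Length of stay defined as the duration of ICU admission from the start of mechanical ventilation and until death or ICU discharge". The item just before it is a separate mortality outcome: "ICU mortality defined as the mortality from randomisation and until death or ICU discharge".

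Statistical considerations sets one rule for primary and secondary outcomes alike: "comparison made by independent samples t-test, or appropriate non-parametric testing if not normally distributed". It adds a general line: "Complementary analysis will be performed using Kaplan-Meier curves". It does not say which outcomes the curves cover or how death enters them.

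The Discussion returns to the two outcomes together: "Although not powered to detect differences between groups, it will also investigate the length of stay at the ICU and patient mortality".

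**The concern.** Death and live discharge are opposite results of an ICU stay, yet the definition lets either close the interval and records only its length. The test then sees the number of days and not how the stay ended. If one arm has earlier deaths, or extra deaths that cut short stays which would have run longer, its recorded stay falls. A reader who takes a shorter stay as good news would then credit that arm with a gain produced by deaths. Conversely, an arm that keeps patients alive long enough to recover could appear to do worse on this outcome.

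The outcome definition is stated in the article, and so is the type of test. The problem comes from those two stated rules together, not from a detail left out.

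**Working it through.** **Does anything in the article separate the two endings?**

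- The definition ends the stay at whichever comes first, death or discharge.
- The comparison rule (t-test or non-parametric test) has no provision for death.
- The Kaplan-Meier line does not help. Under this definition death is itself an endpoint, so the curve drops faster in an arm with earlier deaths.
- ICU mortality is a separate outcome, and nothing joins it to stay.

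**The plan's own figures.** The article gives none for ICU stay or ICU mortality. The only design figure used here is 137 patients per arm, from Statistical considerations, where it is derived for duration of ventilation. That figure is broadly reproducible: a 2-day difference with the average of SDs 7.0 and 4.9 (5.95) gives 139 per arm, two-sided. The present point does not depend on it.

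**Model A: death at a fraction of the would-be stay.** All inputs are assumptions. Both arms have the same would-be stay, with mean M = 10 days. A share p die, each at a fraction f of the stay they would otherwise have had.

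Mean recorded stay = M × (1 − p × (1 − f))

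Difference between arms = −M × (p₁ − p₀) × (1 − f)

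With p₀ = 20%:

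| f | p₁ = 25% | p₁ = 30% | p₁ = 35% |
|---|---|---|---|
| 0.3 | −0.35 | −0.70 | −1.05 |
| 0.5 | −0.25 | −0.50 | −0.75 |
| 0.7 | −0.15 | −0.30 | −0.45 |
| 1.0 | 0 | 0 | 0 |
| 1.3 | +0.15 | +0.30 | +0.45 |

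Entries are days, for the arm with more deaths minus the other arm. For example, at f = 0.3 and p₁ = 35%: −10 × 0.15 × 0.7 = −1.05.

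Earlier deaths with equal mortality of 25%: moving f from 0.7 to 0.5 gives 10 × 0.25 × (0.5 − 0.7) = −0.5 days. Moving it to 0.3 gives −1.0 day.

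**Model B: constant hazards.** Live discharge is assumed at 0.08 per day in both arms. Mean stay as defined = 1/(0.08 + death hazard), and ICU mortality = death hazard/(0.08 + death hazard).

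| Death hazard per day | ICU mortality | Mean stay (days) | Shift from first row (days) |
|---|---|---|---|
| 0.02 | 20% | 10.00 | n/a |
| 0.03 | 27% | 9.09 | −0.91 |
| 0.04 | 33% | 8.33 | −1.67 |

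This model can only shorten the stay when deaths are added, so it belongs at the upper end of the range.

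**How often would the planned tests react?** Model A was simulated with lognormal stays (mean 10, SD 9), 137 per arm and 4,000 trials per setting. The last two columns give the share of trials with p < 0.05.

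| Mortality | f | t-test | Mann-Whitney |
|---|---|---|---|
| 20% vs 20% | 0.5 | 5.4% | 5.8% |
| 20% vs 30% | 0.5 | 8.2% | 11.1% |
| 20% vs 30% | 0.3 | 11.1% | 18.2% |
| 20% vs 35% | 0.3 | 19.0% | 34.8% |

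**Does the alternative point the right way?** Under Model B, cumulative incidence of live discharge by day t = [0.08/(0.08 + h)] × (1 − e^(−(0.08 + h)t)), with h the death hazard. At day 10 this is 0.80 × (1 − e^(−1.0)) = 0.51 for h = 0.02 and 0.667 × (1 − e^(−1.2)) = 0.47 for h = 0.04. The arm with more deaths now shows fewer live discharges, not a shorter stay.

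**The case against.** There is a fair case for leaving the definition alone.

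- **Raw stay is a legitimate quantity.** It measures ICU time actually used, and the Introduction cites economic cost as part of the motivation. No section calls a shorter stay an improvement, and the stated hypothesis concerns time to successful extubation. This stands for description. It does not settle the matter for a between-arm test listed among clinical outcomes, where readers will supply the direction themselves.
- **Mortality is reported too.** It runs to the same end point, so an imbalance would be visible, and the Discussion names the two together. This stands in part. With 137 per arm, the power to detect 20% versus 33% mortality is about 0.7, and for 20% versus 27% about 0.3. A moderate imbalance could pass as non-significant beside a shorter stay.
- **The outcome carries little weight.** It is one of more than 20 secondary outcomes, and the article says it is unpowered. This stands, and it limits the importance of the point.
- **The analysis plan may handle it.** Survivor tables and competing-risk analyses are often left there. An unseen plan could add them, but the definition and the type of comparison are already fixed in the article.

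A reader might infer more: that the arm with more deaths must show the shorter stay, or that the outcome always points the wrong way. The documents do not support that. They give no mortality or timing figures, and Model A shows no shift when deaths coincide with the would-be discharge and a reversed one when they come later.

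**Conclusion.** The concern holds in conditional form. As defined and tested, ICU stay is shortened by earlier deaths, and by extra deaths that precede the would-be live discharge. Nothing in the article separates that from faster recovery.

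The size rests wholly on assumed mortality and timing. Model A, with deaths at 30-70% of the would-be stay, gives 0.15-1.05 days. The 1.67 days of Model B needs a doubled death hazard, and even that is only about 1.5 standard errors with 137 per arm (1.67/1.11, taking each arm's SD equal to its mean).

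The primary outcome's result is not touched by this definition. What is at risk is the interpretation of one unpowered secondary outcome. The change is still worth making, because it is specific and cheap and removes a distortion from a planned comparison.

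**What to change.** Make the between-arm comparison time to ICU discharge alive, with ICU death as a competing event, shown as cumulative incidence by arm. Keep raw length of stay, as now defined, as a descriptive resource-use measure. Tabulate it separately for survivors and non-survivors, beside ICU mortality, without a test.

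The cost is one extra analysis and a documented change to how a secondary outcome is analysed, which should be dated and made before the comparative data are seen. No new data are needed: the existing length-of-stay and ICU mortality outcomes already require the time of ICU exit and whether the patient was alive.
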